#### Strategies to improve adherence to interventions {11c}

Study patients will be hospitalized during the period in which they are receiving the study treatment. The investigator of each site will review and record the traceability of the medication administered.

#### Relevant concomitant care permitted or prohibited during the trial {11d}

The concomitant medication recommendations listed in the technical data form for ciprofloxacin should be taken into consideration.

Special attention should be paid to drugs that prolong the QT interval (class IA and III anti-arrhythmics, tricyclic antidepressants, macrolides, and antipsychotics) as well as tizanidine, methotrexate, and theophylline.

The concomitant medication recommendations listed in the technical data form for fosfomycin will be taken into consideration.

#### Provisions for post-trial care {30}

The health professionals participating in this clinical trial belong to the Spanish National Health System. These are non-commercial studies where the sponsor is a non-profit foundation, FINBA. The trial subjects do not receive any compensation.

#### Outcomes {12}

The primary endpoint is febrile neutropenia requiring antibacterial treatment.Fever is defined as a single oral temperature of 38.3 °C or a temperature of 38 °C sustained over a 1-h period.

If the patient is receiving any medication highly likely to induce fever or has previously received a transfusion, at least one positive culture or infectious focus will be required for fever to be attributed to infection.

When febrile neutropenia occurs and infection is suspected, prophylactic antibiotics will be discontinued and evaluation and therapy will be administered according to standard and local guidelines.

Secondary endpoints are as follows:Documented infections. They will be classified according to Han’s criteria in one of these categories: microbiologically documented infection (bacterial viral or fungal), mixed infection, clinically documented infection, and possible infection (fever of unknown origin).The amount of concomitant antibiotics prescribed in addition to prophylactic drugs will be measured as a ratio of antibiotic days per days of hospitalization. Antibiotics will be classified according to the watch/reserve classification (21).Overall survival will be defined as the time from the day of randomization to the date of death (whatever the cause of death) or to the completion of the study. Fever-free survival will also be determined.

Safety will be assessed by the incidence, severity and type of adverse events (AEs), and by the microbiological assessments:

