### Criteria for discontinuing or modifying allocated interventions {11b}

Treatment will be interrupted when any of the following events occurs first:

Febrile neutropenia requiring antibacterial treatment (main end point of the study).Absolute neutrophil count (ANC) > 0.5 × 10^9^/L.If the subject fails to achieve more than 0.5 × 10^9^/L neutrophils, treatment will end when more than 60 days have elapsed since the onset of neutropenia or on the first day of the next chemotherapy cycle (whichever occurs first).Death

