### Sample size {14}

The reviewed clinical trials and meta-analyses have consistently shown that 65% of patients receiving prophylactic the fluoroquinolones levofloxacin and ciprofloxacin will develop infectious fever (2,17,18) which is consistent with success rate of 35%. Considering that the actual rate of resistance to fluoroquinolones is established to be around 50%, we anticipate a success rate of 17% and 30% in the active control and active and experimental control arms, respectively.

If a non-inferiority margin of 5% is defined, one hundred and thirty-four patients (67 in each arm) will be needed to demonstrate non-inferiority of fosfomycin versus ciprofloxacin with 80% potency and an alpha level of 0.05.

Considering that 15% of the enrolled patients will be ineligible or unable to be evaluated, the maximum number of study participants will be 156: 78 patients in each arm.

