## Statistical methods

### Statistical methods for primary and secondary outcomes {20a}

This phase 3 trial will compare the efficacy of fosfomycin with that of ciprofloxacin in preventing the occurrence of at least one episode of neutropenic fever of infectious origin in a randomized non-inferiority design.

The primary endpoint is febrile neutropenia of infectious origin. This analysis will be performed in the intention-to-treat (ITT) and in the per-protocol population (PP). The ITT population is defined as all patients who are eligible and randomized. The PP population consists of all patients who do not have major protocol deviations, as determined by the study PI, and have received prophylactic drugs for at least of 24 h.

The rate of febrile neutropenia will be compared between the 2 arms with a chi-square test with 2-sided alpha of 0.05. The difference in the proportion and the associated 95% CIs will be provided. If, within either patient arm, the data suggest a possible difference in baseline incidence between the randomization strata, we will consider Cochran-Mantel–Haenszel test to examine the association between the incidence of febrile neutropenia and the study treatment with adjustment for the randomization strata. Logistic regression models will be performed to evaluate the treatment effect on the incidence of febrile neutropenia adjusting for stratification and other baseline patient characteristics.

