Our study will have some limitations: first it will be open, which might favor the early termination of prophylaxis in the fosfomycin arm. However, a strict definition of febrile neutropenia of infectious origin has been specified in the protocol, which excludes transfusional associated fever or fever related to cytarabine (a common chemotherapy drug used in acute myeloid leukemia) or other drugs. Second, this is not a superiority trial, but a non-inferiority one, because it would have been unethical to conduct a trial comparing fosfomycin with placebo. Notwithstanding the limitations of this type of design [20], if fosfomycin proves to be equally effective and safer than ciprofloxacin, it will open the possibility of having more than one family of prophylactic drugs, making it possible to reduce the resistance associated with continued exposure to the same antibiotic and to select one treatment or another based on bacterial ecology and local resistance.

In summary, the present project addresses an extremely important health problem by evaluating the efficacy of fosfomycin, a broad-spectrum antibiotic with a better safety profile and a lower potential of resistance induction than ciprofloxacin, in the prevention of infections in hematological patients with high-risk neutropenia. The battery of microbiological studies that will be carried out will allow us to evaluate prospectively, for the first time, the microbiological safety of both pharmacological strategies and the selection of MRGNB in each arm and will generate valuable information on the way in which changes that occur in the fecal microbiome of the patients throughout the treatment modify the evolution of the studied diseases.

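### The transfusion condition in the fever-attribution rule has no time limit or causal link, and the two wordings of the primary endpoint then classify the same treated fever in opposite ways

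*Protocol article*

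**What the plan says.** All references are to the protocol article.

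- Outcomes {12} opens with a treatment-based endpoint: "The primary endpoint is febrile neutropenia requiring antibacterial treatment". The discontinuation criteria {11b} repeat it: "Febrile neutropenia requiring antibacterial treatment (main end point of the study". Neither wording requires the fever to be attributed to infection.
- Outcomes {12} then adds an attribution rule for two groups. One is patients currently on a drug likely to cause fever. The other is any patient who "has previously received a transfusion, at least one positive culture or infectious focus will be required for fever to be attributed to infection". The drug half is tied to the present. The transfusion half covers any past transfusion.
- Statistical methods {20a} states the endpoint with attribution built in: "The primary endpoint is febrile neutropenia of infectious origin". The hypothesis under Objectives {7} also speaks of fever of infectious origin.
- The Discussion presents the definition as a safeguard against open-label bias, and as one "which excludes transfusional associated fever or fever related to cytarabine".
- The secondary endpoint in Outcomes {12} keeps unexplained fever as an infection category: "clinically documented infection, and possible infection (fever of unknown origin").
- Sample size {14} starts from the statement that "65% of patients receiving prophylactic the fluoroquinolones levofloxacin and ciprofloxacin will develop infectious fever". It then plans success rates of 17% (ciprofloxacin) and 30% (fosfomycin), a 5% margin and 67 patients per arm.

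**The concern.** The stated aim is to keep fever caused by a transfusion out of the primary endpoint. The rule as written reaches further. It applies to every later fever in anyone transfused beforehand, whether hours or weeks earlier. Two patients with identical unexplained, treated fevers are then classified differently only because one of them has a transfusion on record.

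Whether this changes the primary result depends on which endpoint wording governs, and the document uses both. Under the infectious-origin wording, the unexplained fever of a previously transfused patient is a success, even though {11b} calls that fever, once treated, the main endpoint and the reason prophylaxis stops. Under the treatment-based wording it is an event.

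The stake is larger in a non-inferiority trial with a fixed absolute margin. If both arms lose the same proportion of events, a true difference shrinks towards zero while the margin stays at 5 points. As an illustration, a true excess of 8 points with fosfomycin and 45% of events reclassified gives an expected difference of 8 × (1 − 0.45) = 4.4 points, inside the margin.

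**Working it through.** **Step 1. One patient, four statements.** Neutropenic fever treated with antibacterials, no positive culture, no focus, a transfusion at some earlier time, no fever-inducing drug.

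| Section | Classification |
|---|---|
| Outcomes {12}, opening; criteria {11b} | Primary event |
| Outcomes {12}, attribution rule, with Statistical methods {20a} | Not attributed to infection, so a success |
| Discussion | Excluded only if the fever is transfusion-associated; an earlier transfusion alone is not enough |
| Outcomes {12}, secondary endpoint | Fits the category for fever of unknown origin, listed as possible infection |

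The statements do not agree, and nothing in the article ranks them.

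**Step 2. Reproduce the planned sample size.** Event rates are 1 − 0.17 = 0.83 and 1 − 0.30 = 0.70. The summed variance is 0.83 × 0.17 + 0.70 × 0.30 = 0.3511. The distance to the margin is 0.13 + 0.05 = 0.18.

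n = (1.645 + 0.842)² × 0.3511 / 0.18² = 67.0 per arm at one-sided 5%. This matches Sample size {14}, with power 80.0%. At one-sided 2.5%, which corresponds to the 95% confidence interval in {20a}, 67 per arm has 70.1% power. Both levels are shown below.

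**Step 3. What literal use could do.** The document gives neither of two inputs, so both are assumptions:
- t = share of febrile patients with any earlier transfusion
- u = share of fevers with no culture or focus

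The reclassified share of ciprofloxacin events is t × u. A third assumption is how the arms lose events:
- *Proportional loss:* both rates are multiplied by (1 − t·u), so the difference shrinks.
- *Equal absolute loss:* both arms lose 83 × t·u percentage points, so the 13-point difference stays.

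Power = Φ((difference + 0.05)/SE − z), with SE = √(summed variance/67).

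Worked line for t = 0.7, u = 0.3, proportional loss: the factor is 0.79, events are 0.6557 and 0.5530, the difference is 0.1027 and the summed variance is 0.4729. SE = √(0.4729/67) = 0.0840. Then 0.1527/0.0840 − 1.645 = 0.173, and power is 56.9%.

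| t | u | t·u | Proportional: events %, cipro / fosfo | Power % (5% / 2.5%) | Equal absolute: events %, cipro / fosfo | Power % (5% / 2.5%) |
|---|---|---|---|---|---|---|
| – | – | 0 | 83.0 / 70.0 | 80 / 70 | 83.0 / 70.0 | 80 / 70 |
| 0.25 | 0.3 | 0.075 | 76.8 / 64.8 | 71 / 59 | 76.8 / 63.8 | 74 / 63 |
| 0.7 | 0.3 | 0.21 | 65.6 / 55.3 | 57 / 44 | 65.6 / 52.6 | 69 / 57 |
| 0.5 | 0.5 | 0.25 | 62.3 / 52.5 | 54 / 41 | 62.3 / 49.3 | 68 / 56 |
| 0.95 | 0.5 | 0.475 | 43.6 / 36.8 | 40 / 29 | 43.6 / 30.6 | 70 / 59 |
| 1.0 | 0.6 | 0.60 | 33.2 / 28.0 | 36 / 25 | 33.2 / 20.2 | 77 / 66 |
| 0.95 | 0.7 | 0.665 | 27.8 / 23.5 | 34 / 24 | 27.8 / 14.8 | 82 / 73 |

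The event rate falls in every row. Power falls steeply under proportional loss. Under equal absolute loss it falls modestly and ends slightly above plan in the last row.

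**The case against.** The strongest reply is that the sections, read together, point to a sensible meaning. The Discussion names transfusion-associated fever. The neighbouring clause in Outcomes {12} concerns a drug being given at the time. The category "possible infection (fever of unknown origin") would be of little use if most unexplained fevers were barred from attribution. A window in hours is also detail that an article may leave to the full protocol. Outcome assessors are blinded ({17a}), and fever data are fully monitored ({23}), which limits unchecked divergence between sites.

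Part of this stands. The likely intent is the narrow one, and it cannot be said that sites are in fact classifying patients differently. It does not remove the point. The article does not merely omit a window; it states a rule broader than the purpose it gives. Blinding and source verification cannot choose between two readings of the definition.

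A reader might infer a stronger claim: that the rule catches nearly every patient, decides most of the primary outcome and takes power well below plan. The document does not support that. It gives no transfusion frequency and no share of unexplained fevers. The steep power loss also needs both arms to lose the same proportion of events, which is nowhere stated. Nor can it be said that the planning rates included unexplained fever: Sample size {14} says only infectious fever, and the cited trials are not available here.

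**Conclusion.** The point holds as a defect of definition. The transfusion condition is unbounded and broader than the Discussion says is intended. Combined with two wordings of the primary endpoint, it lets the same treated fever count as an event or as a success. This follows from the text alone and needs no assumed rate.

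The size is unknown. That many patients are affected is plausible in first intensive chemotherapy or transplant, but it is an assumption. In the scenarios above, power at 67 per arm and one-sided 5% runs from 34% to 71% with proportional loss and from 68% to 82% with equal absolute loss, against 80% planned. These figures show how much the result could depend on the reading; they are not an estimate of harm. It should be settled before the analysis, because it decides who counts as a primary event.

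**What to change.** 1. In Outcomes {12}, limit the transfusion condition to fever linked in time to a transfusion. The sponsor sets the interval, and it applies equally in both arms.
2. Reconcile Outcomes {12}, the discontinuation criteria {11b}, Statistical methods {20a} and the Discussion into one primary endpoint definition. It should say outright whether treated fever of unknown origin counts. That choice is the sponsor's and should be made openly, since bounding the transfusion condition does not settle it.
3. Have the blinded assessors apply the definition to all patients before the analysis, including those already enrolled (106 of a planned 156 when the article was submitted).
4. Report the literal rule, with any earlier transfusion triggering the requirement, as a sensitivity analysis.

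The cost is small: a revised endpoint definition, the matching edits in the other sections, and transfusion dates and times for febrile patients from hospital records. No new patients, visits or procedures are needed.

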## Microbiological assessments

Rate of patients colonized by GNMRB as determined by surveillance and metagenomic sequencing.Changes in the gut microbiome produced in both groups.

### Participant timeline {13}

The flow chart for the study and the schedule visits and assessments at different points in the study protocol are described in Table 2.

**Table 2 Tab2:** Schedule of visits and assessments at different points of the study protocol

Procedures	Screening visit	Day^a^ 1	Day 8 ± 1	Day 15 ± 2	Day 22 ± 2	Day 29 ± 2	End of treatment
Informed consent form	X						
Inclusion/exclusion criteria	X						
Randomization		X					
Demographic data	X						
Medical history	X						
Size	X						
Weight	X	X	X	X	X	X	X
Physical examination: vital signs	X	X	X	X	X	X	X
ECOG	X						X
Electrocardiogram	X	X	X	X	X	X	X
Study treatment		x	x	x	x	x	
Hemogram	X	X	X	X	X	X	X
Biochemistry	X	X	X	X	X	X	X
Coagulation	X	X	X	X	X	X	X
Pregnancy test	X						
Concomitant medication/antimicrobials	X	X	X	X	X	X	X
Adverse effects		X	X	X	X	X	X
Microbiological culture	X	X	X	X	X	X	X
Stool sample for microbiome analysis	X						X^b^

^a^When less than 72 h have elapsed between the screening visit and day 1, it will not be necessary to repeat the electrocardiogram or laboratory studies, including microbiological studies

^b^In case the patient is unable to collect stool before receiving the first dose of empirical antibacterials, a rectal exudate will be taken with a swab

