**Methods:**

A phase III randomized, controlled, clinical trial, open-label parallel-group with a 1:1 ratio, aimed to demonstrate the non-inferiority of oral fosfomycin versus oral ciprofloxacin for febrile neutropenia prevention in patients with acute leukemia (AL) or hematopoietic cell transplant (HSC) receptors. Weekly surveillance cultures are planned to detect gut colonization. Changes in fecal microbiome at the beginning and end of prophylaxis will also be analyzed.

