### Eligibility criteria {10}

Candidate selection will be performed in 2 different settings depending on the therapeutic procedure:In subjects with a suspected diagnosis of acute leukemia, where the diagnosis of the neoplasm is made as an inpatient, the selection will take place once the diagnosis has been confirmed and prior to the start of intensive chemotherapy.In HSCT recipients, selection will take place on an outpatient basis during the pre-transplant evaluation.

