### Plans for collection, laboratory evaluation, and storage of biological specimens for genetic or molecular analysis in this trial/future use {33}

All study subjects will be screened for MDRGN gut colonization by microbiological culture at the first visit and weekly thereafter during the neutropenic period, until study completion. In each participating center, rectal exudates will be collected in ESwab™ (Copan Diagnostics Inc., Murrieta, CA) that will be sent to the microbiology laboratories for culture in selective media for MDRGN, according to the recommendations of the Spanish Society for Infectious Diseases and Clinical Microbiology (SEIMC) (22,23), specifically in CHROMagar™ *Acinetobacter* (Biomerieux, Marcy l’Etoile, France), CHROMagar™ *P. aeruginosa* (Biomerieux), CHROMagar ™ ESBL (Biomerieux), and CHROMagar™ CARBA SMART (Biomerieux) and in Columbia Agar plate (Biomerieux) as a growth and sample quality control. The isolates recovered in the selective media will be identified by MALDI-TOF/MS (Bruker Daltonics, Bremen, Germany), and the antimicrobial susceptibility testing will be performed using the Microscan system (Beckman Coulter, Brea, CA) and interpreted according to the European Committee on Antimicrobial Susceptibility Testing (EUCAST) guidelines. Bacterial samples and isolates will be stored at – 80 °C.

The clinical trial includes a substudy in a population of 30 subjects, representative of the two treatment arms, both colonized and non-colonized according to the conventional microbiological techniques results. Two samples from each of these subjects will be recovered between those processed for culture (stored at – 80 °C) at the baseline visit and at the end of the study. In these samples, the evolution of the resistome will be investigated using “shotgun” metagenomic sequencing techniques. These results will be compared with those obtained by culture.

The patient’s microbiome evolution will be studied by metataxonomic sequencing. For this purpose, a fecal sample will be collected from each study subject at the baseline visit and at the end of the study.

Figure 1 shows schematically the clinical and microbiological study planning.

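### The microbiome change pairs a screening stool with an end sample that becomes a rectal swab mainly in febrile patients, which ties sample type to the primary outcome

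*Protocol article*

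**What the plan says.** **The aim.** The abstract (Methods) states: "Changes in fecal microbiome at the beginning and end of prophylaxis will also be analyzed". The Microbiological assessments section lists "Changes in the gut microbiome produced in both groups" as an assessment.

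**The samples.** In Table 2 (Participant timeline {13}) the row "Stool sample for microbiome analysis" is marked at screening and at end of treatment, with nothing on Day 1. Footnote b is attached to the end mark only: for a patient "unable to collect stool before receiving the first dose of empirical antibacterials, a rectal exudate will be taken with a swab". Section {33} mentions no swab for this analysis: "a fecal sample will be collected from each study subject at the baseline visit and at the end of the study".

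**What triggers the swab.** Section {11b} ends prophylaxis at febrile neutropenia that needs antibacterials and labels this the main endpoint. Section {18b} places the end-of-treatment visit at the last dose of study drug.

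**When the baseline is taken.** Section {10} states: "In HSCT recipients, selection will take place on an outpatient basis during the pre-transplant evaluation". Leukemia patients are selected as inpatients, after diagnosis and before intensive chemotherapy. Footnote a to Table 2 waives the Day 1 repeat of ECG, laboratory and microbiological studies when less than 72 h have passed since screening. Culture is therefore repeated on Day 1 after a longer gap, but the microbiome stool is not.

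**What else is stored.** Section {33} collects rectal exudates for culture at the first visit and weekly. It draws the samples for the 30-patient resistome substudy from this material, stored at –80 °C.

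**The concern.** A change score is interpretable only if both samples measure the same thing. Under footnote b, some patients contribute stool minus stool and others swab minus stool. What sorts them is whether empirical antibacterials came before a stool, which mostly means whether they had the primary event. Any systematic difference between swab and stool then appears as microbiome change in febrile patients.

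This bears on what the trial wants to learn. The Background cites low diversity as a risk factor for infection in acute leukemia. The Discussion says the microbiome data will show how changes under treatment modify the course of disease, and it expects larger changes under fluoroquinolones. An artefact linked to fever would enter the first of these questions directly and the second indirectly.

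The baseline raises a separate issue. The abstract refers to the beginning of prophylaxis, but the stool is taken at screening. Any change between screening and the first dose is counted as change under prophylaxis, and the setting of that sample differs between leukemia and HSCT patients.

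**Working it through.** The plan gives no figure for the microbiome comparison, so there is none to reproduce. The check uses the plan's fever assumptions and varies what is not given.

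**Inputs from the documents (Sample size {14})**
- Anticipated success: 17% ciprofloxacin, 30% fosfomycin.
- Anticipated fever: 1 − 0.17 = 0.83 and 1 − 0.30 = 0.70, a difference of 0.13.
- Planned size: 78 per arm.

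**Inputs not in the documents (assumed)**
- *s*: share of febrile patients with no stool before the first empirical dose.
- *b*: shift of a swab relative to stool, in SD units of the change score.
- Fever-free patients give stool at both ends. This is an approximation (see the objection).

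**Step 1. Patients the rule could reach.** 0.83 × 78 = 64.7 and 0.70 × 78 = 54.6, or about 65 and 55 per arm.

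**Step 2. Share of stool-to-swab pairs = fever rate × *s*.**

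| *s* | Ciprofloxacin | Fosfomycin | Difference (points) | Patients of 78 |
|---|---|---|---|---|
| 0.25 | 20.8% | 17.5% | 3.3 | 16 vs 14 |
| 0.50 | 41.5% | 35.0% | 6.5 | 32 vs 27 |
| 0.75 | 62.3% | 52.5% | 9.8 | 49 vs 41 |
| 1.00 | 83.0% | 70.0% | 13.0 | 65 vs 55 |

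**Step 3. Size of the artefact.** A mixed pair has change + *b*, and a stool pair has change alone.
- Between arms: 0.13 × *s* × *b*. At *s* = 0.5, *b* = 0.5: 0.13 × 0.5 × 0.5 = 0.03 SD. At *s* = 1, *b* = 1: 0.13 SD.
- Febrile versus fever-free: *s* × *b*. In the same two cases, 0.25 SD and 1 SD.
- With equal fever rates the between-arm term is 0, while the febrile versus fever-free term is unchanged.

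**Step 4. Like-with-like pairing.** In a swab-to-swab pair the shift enters both samples: (change + *b*) − *b* = change, provided the shift is the same at both times.

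**Step 5. Baseline timing.** Screening precedes randomization, which is 1:1 and stratified by underlying disease (sections {8} and {31}-related allocation text, {16a}). The gap before Day 1 therefore has the same expected distribution in both arms. It may differ between leukemia and HSCT patients. No maximum interval is stated, so its effect cannot be sized.

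**The case against.** Footnote b has a good reason behind it: it secures a sample before empirical antibacterials. Without it, febrile patients would have a post-antibiotic sample or none, and either would also be linked to outcome. That stands. The rule should be kept, and only the baseline it is compared with needs to change.

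How sample type is handled in the model could sit in an analysis plan or laboratory manual that is not shown. That also stands, so the point rests on the sampling rule itself and on the mismatch between Table 2 and section {33}.

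A reader might infer more than the documents support:
- *That swabs occur only in patients with the primary event.* The trigger is empirical antibacterials. Under section {12}, fever in a patient on fever-inducing medication or after a transfusion counts only with a positive culture or a focus. Such a patient could be treated, and swabbed, without meeting the endpoint.
- *That a material part of any arm difference must be artefact.* The link to arm exists only if fever rates differ. It is capped at 13 points on the protocol's own rates, and needs a real stool-swab difference that the documents neither state nor size.
- *That the early baseline biases the comparison of arms.* Stratified randomization after the sample rules this out in expectation.
- *That sample type differs by disease group.* No figure in the documents shows this.

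The resistome substudy is not affected by the sample-type mismatch, since it takes stored culture samples at both times.

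**Conclusion.** The point holds in limited form. As written, the plan produces stool-to-swab pairs mainly in patients who reach the primary event, and section {33} does not acknowledge them. The main consequence is for analyses relating microbiome change to fever: an artefact of *s* × *b*, for example 0.25 SD if half of febrile patients are swabbed and swab and stool differ by half an SD. The consequence for the comparison of arms is indirect and small, about 0.03 SD in that scenario and 0.13 SD with both values set to 1. Both *s* and *b* are assumptions. If swab and stool give the same profile, there is no artefact.

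The screening baseline does not match the stated start of prophylaxis. It affects the reading of within-patient change and of differences between disease groups, by an amount that cannot be derived.

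This concerns a microbiological assessment listed under safety. The primary analysis is untouched.

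**What to change.** 1. Reconcile section {33} with footnote b, so that both state when the end microbiome sample is stool and when it is a swab.
2. When the end sample is a swab, use the patient's stored baseline rectal exudate as its pair: the Day 1 swab where one was taken, otherwise the screening swab. Footnote a means that not every patient has a Day 1 swab.
3. Compute no change across a stool-swab pair. Report stool-stool and swab-swab pairs, with a sensitivity analysis by sample type. Stool-stool pairs alone would not suffice, because that subset is partly selected by outcome.
4. Record sample type and the screening-to-Day-1 interval for every patient, and describe the baseline as a screening sample where that is what it is.

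Moving the baseline stool to Day 1 now is not advised. Trial status reports 106 of the planned 156 patients already recruited, so early and late recruits would have different baselines.

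**Cost.** One extra stored baseline swab is sequenced per affected patient: 78 × (0.83 + 0.70) × *s*, or about 30, 60 or 90 swabs for *s* = 0.25, 0.50 or 0.75. No new patient procedure is needed. This assumes that enough stored material remains after culture and the substudy. The work must be done before the trial ends, because section {26b} states that no samples are kept afterwards.
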